### Randomisation

When patients want to participate in the trial and meet the requirements, a research assistant who reviews and explains the study collects the patient’s basic demographic information and previous clinical data. Eligibility of the patient is ascertained, followed by provision of the written consent form. Before randomisation, the patients must have reassessed their hearing status with an otoscopic examination, hearing threshold tests (air conduction hearing thresholds measured at 250–8000 Hz, bone conduction hearing thresholds measured at 500–4000 Hz), word recognition scores (WRSs) and ear-specific immittance measurements (including tympanometry, static immittance and acoustic reflex measures). These measures can assess the patient’s baseline hearing state and exclude conductive hearing loss. According to the classification standard of hearing loss degree published by the World Health Organization in 1997, the average values of hearing thresholds of 500, 1000, 2000 and 4000 Hz were calculated and then divided into categories of mild (26–40 dB hearing loss [HL]), moderate (41–60 dB HL), severe (61–80 dB HL) and profound (≥ 81 dB HL). Patients were stratified by gender, age and degree of hearing loss. Patients of the same gender, with age differences within 3 years and with the same degree of hearing loss were classified in the same stratification.

A statistician who is not part of the clinical intervention uses the Statistical Package for the Social Sciences (SPSS) 21.0 (IBM, Chicago, IL, USA) to generate a randomisation code. This code is embedded into serially numbered, opaque envelopes. After a participant completes the baseline measures, and when the same stratification reaches two or an even number of patients, another research assistant opens the next envelope in the series to determine the participant group allocation. Patients in the same stratification are randomised for the two treatments with a 1:1 ratio.

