### Sample size

To the best of our knowledge, no randomised pilot study has been conducted to assess the effectiveness of lifestyle changes on ISSNHL. Therefore, we are not able to calculate the sample size based on previous studies. On the basis of our retrospective analysis (unpublished) and clinical experience, the efficiency ratio of the intervention group is conservatively estimated to be 50%, and the natural recovery rate over 2 weeks is 10% [9]. Using a formula [23] to calculate the sample size of optimal treatment in the clinical trial and considering α = 0.05, β = 0.1, by the table of normal distribution quantifiers *U*_α(0.05)_ = 1.65, *U*_β(0.1)_ = 1.28, we require a patient sample size of 23 per group. We allow for a 20% loss to follow-up (approximately 10 cases), with a total sample size of 56 patients (28 per group) in the study.
$$ {\displaystyle \begin{array}{l}n={\left( U\alpha + U\beta \right)}^22P\left(1-P\right)/\left({P}_1-{P}_0\right)2,\\ {}P=\left({\mathrm{P}}_1+{\mathrm{P}}_0\right)/2\times 100\%,\end{array}} $$

*P*_0_: original efficacy, *P*_1_: expected efficacy.

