### Statistical analysis

Data are analysed using SPSS V.21.0 (Chicago, IL, USA), with the significance level set at 0.05 (two-tailed) by statisticians who are independent of the research team. Patient baseline characteristics are summarised by treatment arm by employing appropriate summary statistics to assess baseline comparability only. Data analysis is conducted with the intention-to-treat (ITT) principle and a per-protocol (PP) analysis. To ensure the comparability of baseline conditions between the two groups and allow the presence of noncompliant patients, the ITT population consists of all randomised participants. In addition, at least one follow-up will be recorded after the intervention. According to the patients’ actual lifestyle adjustment after random grouping, the PP analysis studies the patients who completed the trial and did not violate the protocol. This process is an explanatory, supplementary analysis, contributing to study objectivity. We calculate the effective rates at 1 and 3 months for the primary outcome and compare the intervention and control groups by using the χ^2^ test. For secondary outcomes, continuous variables, including THI, visual analogue scale and WRS, are compared between the two groups at all follow-up time points by using a *t* test or the Wilcoxon signed-rank test as appropriate. Categorical variables, such as different degrees of hearing loss, are compared using the χ^2^ test or Fisher’s exact test. For dropout analysis, we use multiple imputations for ITT analysis. A sensitivity analysis is performed to assess the effect of missing data assumptions.

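### Randomisation is stratified by sex, age and hearing-loss grade but the primary χ² test ignores the strata: valid, yet conservative and a few points short of power if those factors predict response

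*Protocol article*

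**What the plan says.** The Randomisation section of the protocol article states: "Patients were stratified by gender, age and degree of hearing loss". The strata are narrow: "Patients of the same gender, with age differences within 3 years and with the same degree of hearing loss were classified in the same stratification". The grades are the four WHO classes, mild to profound, based on the mean threshold at 500 to 4000 Hz. Allocation waits until the stratum holds enough patients ("when the same stratification reaches two or an even number of patients"), and then "Patients in the same stratification are randomised for the two treatments with a 1:1 ratio". In practice this comes close to randomising matched pairs.

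The Statistical analysis section computes effective rates at 1 and 3 months "for the primary outcome and compare the intervention and control groups by using the χ^2^ test", at a two-sided 5% level. It names no stratified, matched or covariate-adjusted analysis of the primary outcome. The Sample size section uses an unstratified two-proportion formula and assumes no gain from stratifying.

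**The concern.** The plain χ² variance allows for chance imbalance between the arms on sex, age and grade. The allocation scheme has removed that imbalance by design. Where a balanced factor predicts response, the variance used is larger than the variance that applies, so the p-value and any interval built on it are conservative.

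Some prognostic value is plausible. The sponsor chose these factors for unusually tight balancing, and a patient with a mean loss of 26 to 40 dB may have limited room for a 15 dB gain. In a trial of 56 patients a few points of power are worth keeping, especially as the 50% response assumed for the intervention rests on unpublished data and clinical experience and the true effect may be smaller.

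**Working it through.** **1. The plan's own figure.** Inputs from the Sample size section: P1 = 0.50, P0 = 0.10, P = 0.30, quantiles 1.65 and 1.28.

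n = (1.65 + 1.28)² × 2 × 0.3 × 0.7 / 0.4² = 8.585 × 0.42 / 0.16 = 22.5, so 23 per group. Then 23 × 1.2 = 27.6, so 28 per group and 56 in total. The stated figures reproduce, and stratification does not enter them.

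**2. How far the χ² variance can be off.** Take n matched pairs and a common response rate p in both arms. The χ² test uses a variance of 2p(1−p)/n. If two partners' outcomes have correlation ρ through the shared stratum, the true variance is 2p(1−p)(1−ρ)/n. The true standard error is therefore √(1−ρ) times the one used, and the actual two-sided level is about 2Φ(−1.96/√(1−ρ)). If only grade matters, ρ = Var(grade-specific rates) / [p(1−p)].

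The article gives no response rates by grade. The gradients below are assumptions, with four equally common grades.

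| Assumed rates by grade | p | Var | ρ | √(1−ρ) | Approximate level | Simulated level, χ² / stratified |
|---|---|---|---|---|---|---|
| no gradient | 10% | 0 | 0 | 1 | 5% | 5.2% / 5.1% |
| 3/6/11/20% (moderate) | 10% | 0.00415 | 0.046 | 0.977 | 4.5% | 4.6% / 4.7% |
| 1/3/10/26% (strong) | 10% | 0.00965 | 0.107 | 0.945 | 3.8% | 4.0% / 4.4% |
| 5/15/36/64% (strong) | 30% | 0.05105 | 0.243 | 0.870 | 2.4% | 2.6% / 4.9% |

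Example, last row: (0.0025 + 0.0225 + 0.1296 + 0.4096)/4 − 0.09 = 0.05105, and 0.05105/0.21 = 0.243. The formula and the simulation (28 pairs) agree. The χ² test is conservative when grade is prognostic, and clearly so only when the response rate without effect is well above the plan's 10%.

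**3. Power.** Simulation of matched pairs with a common odds ratio, 40,000 runs per setting, two-sided 0.05. Plain χ² is compared with a Cochran-Mantel-Haenszel (CMH) test over the four grades, without continuity correction.

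| Setting | Not prognostic | Moderate | Strong |
|---|---|---|---|
| 50% vs 10%, 23 pairs | 88.1 / 87.6% | 88.9 / 90.3% | 90.4 / 94.0% |
| 50% vs 10%, 28 pairs | 93.9 / 93.8% | 94.4 / 95.3% | 95.2 / 97.2% |
| 35% vs 10%, 28 pairs | 62.3 / 63.0% | 62.8 / 66.3% | 63.1 / 71.3% |

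(χ² / CMH.) At the planned effect, CMH differs from χ² by −0.5 to +3.6 points with 23 pairs (87.6 − 88.1; 94.0 − 90.4) and by −0.1 to +2.0 points with 28 pairs. At 35% vs 10% it gains 0.7 to 8.2 points.

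**4. How finely to stratify.** Ages 18 to 60 in 3-year bands give about 42/3 = 14 bands, so 14 × 2 sexes × 4 grades = 112 cells for 56 patients. Expected responders at the planned rates are only 23 × 0.6 = 13.8 to 28 × 0.6 = 16.8. A full-stratum model is not workable. One stratum per pair is possible but costs power when the factors do not matter: 84.9% against 88.2% for χ² (50% vs 10%, 23 pairs), and 59% against 62% (35% vs 10%, 28 pairs). It also loses the partner of every dropout. Grade alone avoids both problems.

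**The case against.** The strongest reply is that an unadjusted χ² test after stratified randomisation is valid, that the size of any loss rests on assumptions, and that the larger losses arise away from the plan's own scenario. All of this stands. At 50% vs 10% with 28 pairs the gain is at most about 2 points in these runs, and at a common rate of 10% the two tests have nearly the same level.

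The prognostic argument is also open to challenge. Grade is a four-frequency mean, whereas the primary outcome concerns the impaired frequencies. A mild mean can hide larger losses at those frequencies, so limited room for a 15 dB gain is plausible but not shown. A CMH test by grade alone also leaves sex and age out, so it reflects the randomisation only in part. That is a deliberate compromise, given how few responders are expected.

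Three stronger readings are tempting, and the article does not support them:

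- **Stratifying brings no statistical return.** The power of χ² rises from 88.1% to 90.4% at 23 pairs as grade becomes more prognostic, so part of the benefit of balance is kept.
- **The mismatch takes the trial below its planned power.** The sample size never counted on a gain from stratifying. The 88.1% against the 90% target ("considering α = 0.05, β = 0.1") comes from using the one-sided 1.65 quantile for a two-tailed test, which is a separate matter.
- **False positives are inflated.** The direction is the opposite.

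An unseen analysis plan could add an adjusted supportive analysis. The article nevertheless names the primary test, and that test ignores the allocation scheme.

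**Conclusion.** The mismatch between design and primary analysis is real, and its consequence is conditional. If sex, age or grade predicts response, the unstratified χ² test uses too large a standard error, is conservative, and gives up about 0 to 4 points of power at the planned effect and up to about 8 points at 35% vs 10% with 28 pairs. If they do not, nothing material is lost. These sizes assume four equally common grades, the gradients listed above, complete pairs, and 1:1 allocation achieved within every stratum. The article supplies no figure for prognostic strength. This is a worthwhile improvement at almost no cost, not a flaw that invalidates the result.

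**What to change.** In Statistical analysis, before unblinding:

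- Make the primary test a Cochran-Mantel-Haenszel test stratified by the four baseline hearing-loss grades, two-sided 0.05, without continuity correction.
- Report the Mantel-Haenszel risk difference over the same grades with a 95% CI, so that test and estimate share one stratification.
- Keep the plain χ² test as a sensitivity analysis. An analysis also adjusted for sex and age can be supportive.
- Do not use one stratum per matched pair.

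Cost: one sentence of text, no new data and no more patients, since grade, sex and age are recorded before randomisation. The price is up to about 1 point of power if grade is not prognostic.

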**Methods:**

This study is a clinical randomised trial that involves 56 patients diagnosed with ISSNHL but who have had incomplete recovery after initial management (at least 2 weeks of routine Western medical treatment). The study is performed in accordance with the sudden hearing loss clinical guideline of the American Academy of Otolaryngology–Head and Neck Surgery, published in 2012. Participants are randomly distributed into two groups: the healthy lifestyle modification group based on TCM and the control group (1:1 ratio). Patient follow-up lasts for 3 months. The primary outcome measure is the effective rate of hearing improvement, which is defined as the proportion of patients with at least 15 dB of improvement in the average thresholds of hearing loss frequency. The secondary outcome measures are improvements in word recognition score, Tinnitus Handicap Inventory and visual analogue scale for ear blockage and dizziness. Assessments are made at baseline and after lifestyle modification for 1 and 3 months.

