### Outcome measure evaluation

The outcomes are evaluated at baseline and at 1 month and 3 months after the participant starts the intervention.

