### Secondary outcome measures

Based on the visual analogue scale, the secondary outcomes include improvement of adherence to TCM lifestyle and evaluation of changes in WRS [21], Tinnitus Handicap Inventory (THI) [22] for patients with tinnitus and change in common symptoms, such as dizziness and ear blockage. These outcomes are measured at the first visit and during protocol visits.

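### A paired test (Wilcoxon signed-rank) is named for comparing THI, VAS and WRS between two independent groups

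*Protocol article*

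**What the plan says.** The Statistical analysis section of the protocol article covers the "continuous variables, including THI, visual analogue scale and WRS". They "are compared between the two groups at all follow-up time points by using a" *t* "test or the Wilcoxon signed-rank test as appropriate". The section does not say whether the t test is paired or independent-samples. The primary outcome, the effective rate, is compared between arms by a χ² test.

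On what is being compared, the Secondary outcome measures section speaks of "evaluation of changes in WRS" and of "change in common symptoms, such as dizziness and ear blockage", and the abstract says "The secondary outcome measures are improvements in word recognition score, Tinnitus Handicap Inventory and visual analogue scale for ear blockage and dizziness". A baseline value exists for these: "The outcomes are evaluated at baseline and at 1 month and 3 months after the participant starts the intervention". The Statistical analysis section does not say whether changes or follow-up values enter the tests.

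**The concern.** The signed-rank test ranks the differences within pairs, or the deviations of one sample from a fixed value. The rank test for two separate groups is the Wilcoxon rank-sum (Mann-Whitney) test. The sentence states a between-group purpose and then names a test that cannot serve it unless each patient in one arm has a partner in the other.

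This is a wrong statement in the plan, not a detail left for later. An analyst who follows it must improvise, either by inventing pairs or by substituting another test. Prespecification is meant to remove that choice. The choice would fall on every continuous secondary outcome for which the t test is judged unsuitable.

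**Working it through.** The plan states no figure on this point, so there is none to reproduce. The check sets the sections side by side and then uses simulation under stated assumptions. The 23 per arm used below is the plan's own number before the dropout allowance: (1.65 + 1.28)² × 2 × 0.30 × 0.70 / 0.40² = 22.54, rounded up to 23.

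**1. Does the design supply pairs?** The Randomisation section forms strata by sex, age (to within 3 years) and grade of hearing loss, and allocates 1:1 once a stratum holds two patients or a larger even count. A stratum of two would give a pair. A stratum of four gives two patients per arm, who can be matched across arms in 2! = 2 ways; a stratum of six gives 3! = 6 ways. No section says which matching applies, or that any does. The χ² test for the primary outcome treats the arms as independent.

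**2. Would the arms be equal in size?** The Sample size section allows for 20% loss, so about 28 × 0.8 = 22.4 patients per arm would be observed, equal across arms only by chance. Even if 28 pairs existed, and losses were independent (an assumption), only 0.8 × 0.8 = 0.64 of them, about 17.9, would be complete. The Secondary outcome measures section limits THI to patients with tinnitus, so THI would be missing for some partners even without dropout. A between-arm signed-rank test on 23 versus 21 values returned an error.

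**3. What if unrelated patients are paired by row?** Inputs: independent normal outcomes, two-sided 0.05, 23 per arm, 3,000 runs per setting.
- With no treatment effect, the signed-rank test on arbitrary pairs rejected in 0.046 to 0.055 of trials and the rank-sum test in 0.047 to 0.055.
- In a separate run of 5,000 null trials, the signed-rank test on arbitrary pairs rejected in 0.051 (23 per arm) and 0.047 (28 per arm) with normal data, and in 0.049 and 0.044 with skewed data.
- At an assumed effect of 0.8 SD, power was about 0.70 for the signed-rank test and 0.72 for the rank-sum test.

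Error rate and power are therefore nearly unchanged. What is lost is a unique result, because reordering the rows changes the p-value.

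**4. What if pairs are real?** With an assumed within-pair correlation of 0.3, the rank-sum test had a type I error of about 0.023. The signed-rank test on the true pairs stayed close to nominal (0.050 to 0.059).

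**5. What does the open question about change or follow-up values amount to?** Let r be the correlation between baseline and follow-up, with equal SDs at both times (assumptions). Relative to comparing follow-up values alone, the variance is 2(1 − r) for change scores and 1 − r² for ANCOVA. Power is for 23 per arm and a 0.8 SD effect.

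| | r = 0.3 | r = 0.5 | r = 0.7 |
|---|---|---|---|
| Variance, change score | 1.40 | 1.00 | 0.60 |
| Variance, ANCOVA | 0.91 | 0.75 | 0.51 |
| Power, rank-sum on follow-up values | 0.72 | 0.72 | 0.71 |
| Power, rank-sum on change | 0.59 | 0.72 | 0.91 |
| Power, ANCOVA | 0.79 | 0.85 | 0.95 |

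The choice between change and follow-up values can help or hurt, depending on r. ANCOVA was the most powerful of the three at each value tried.

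**The case against.** The best defence is the allocation scheme. Waiting for an even count within narrow strata resembles matching, multiple imputation could restore partners lost to dropout, and step 4 shows that the rank-sum test is conservative if pairs are real. This stands to the extent that the rank-sum test is not automatically the right replacement. It does not rescue the text, which identifies no pairs and tests the primary outcome unpaired. Nor does dropout imputation supply a THI score for a partner who has no tinnitus.

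It can also be said that this is probably a slip in naming, that the t test is listed first, and that a fuller analysis plan may settle the rest. All of that bears on severity. Baseline adjustment in particular is a matter of efficiency that such a plan may already cover, so it is offered here as an improvement and not as a defect.

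Two stronger readings are tempting, and the document supports neither.
- A reader might infer that baseline values are ignored. The abstract and the Secondary outcome measures section define these outcomes as improvements or changes. What is missing is only a statement of which quantity the tests use.
- A reader might infer that the signed-rank test will be run before versus after within each arm, so that natural recovery is credited to the intervention. The Statistical analysis section states a comparison between groups, and no section proposes a within-arm efficacy test. Any rejection rate for such a test would also rest on a size of change and an SD that the document does not give.

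**Conclusion.** The point holds in limited form: the named non-parametric test does not fit the stated comparison. It cannot be computed when the arms differ in size, and when they are equal it gives an answer that depends on how rows are ordered. It does not inflate the type I error if independent patients are paired arbitrarily. A reader should not conclude that the secondary p-values would be systematically too small.

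Only the continuous secondary outcomes are touched; the χ² test of the primary outcome and the sample size are unaffected. It should be fixed, but it does not threaten the trial's main conclusion. The possible gain from baseline adjustment, a variance reduction of 9% to 49%, rests on the assumed range of r from 0.3 to 0.7, for which the document gives no figure.

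**What to change.** In the Statistical analysis section:
- Replace the signed-rank test with the Wilcoxon rank-sum (Mann-Whitney) test, and call the t test independent-samples.
- If the randomisation strata were meant as matched pairs, define each pair at allocation and use paired methods throughout, including for the primary outcome.
- State whether changes from baseline or follow-up values are analysed.
- Preferably, analyse each follow-up score by ANCOVA on treatment and its own baseline value, and report the adjusted difference with a 95% confidence interval. This is an improvement rather than a correction.

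The cost is wording only. Baseline scores are already scheduled, and the number of patients does not change.

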### Data management

Data accuracy is ensured by completing the paper copies of the case report form. Two independent researchers blinded to the group allocation input the data on an Excel spreadsheet, and the data are checked twice. Data are validated using original case report forms when any discrepancy is discovered. Paper files and electronic documents are stored separately in a locked filing cabinet and on a protected computer. Only the principal researchers are allowed access to the data. Researchers are unable to modify the data. They shall keep the information strictly confidential and shall not disclose it under any circumstances. The researchers shall sign a confidentiality agreement.

## Discussion

ISSNHL, for which the aetiology remains unknown, is an acute disorder that occurs throughout life. Although 49–89% of patients achieve normal hearing through existing therapy with oral or intravenous steroids and with 32—65% spontaneous recovery rates, treatment amongst patients who have incomplete recovery from ISSNHL after failure of initial management remains a problem [8–10]. Some patients are reluctant to receive recommended glucocorticoid treatment because of concerns regarding side effects, contraindications and drug-to-drug interactions. The salvage therapy recommended by the 2012 ISSNHL guidelines is steroid perfusion, which results in hearing improvement ranging from 53 to 90% in the treatment group [24, 25]. The dose and concentration of steroids vary similarly to the criteria used to define hearing improvement.

Previous studies indicated that patients who do not show any improvement within the first 14 days are unlikely to show remarkable recovery afterwards [9, 10], and thus they usually lose hope and discontinue therapy. Therefore, an acceptable and simple therapy is required to improve the effects of refractory ISSNHL for these patients.

TCM has been used for thousands of years and is widely accepted for treating diseases in China. Lifestyle, as part of TCM, has been integrated into the Chinese culture. Tradition and sustained interest in the benefits of a TCM-recommended lifestyle have remained, especially for patients whose conditions have not been effectively treated by Western medicine. We designed this trial to verify that a TCM-based lifestyle can provide help concerning hearing loss and concomitant symptoms amongst patients with ISSNHL. If successful, this intervention may help patients with refractory ISSNHL in China.

The study is designed to explore the efficacy of a TCM-based lifestyle change for patients with ISSNHL who have no or insufficient recovery after initial systematic Western medicine treatment. Although intratympanic steroid perfusion for this kind of ISSNHL has been used in Western treatment, the evidence of its efficacy remains unclear. In this study, the effective rate of hearing improvement is used as the primary outcome measure and is the most common parameter for ISSNHL. Secondary outcome measures include WRS, THI and accompanying symptoms, including dizziness and fullness of the ear. In addition to hearing loss, many people with ISSNHL complain of tinnitus and dizziness. The exact mechanisms that explain the effects of a TCM-based lifestyle change on ISSNHL require further detailed research and discussion in the future.

